**4.4. Administration of Surveys and/or Process:**

**Process for Review of Databases:** We will use data from four different City of Philadelphia departments: Philadelphia Department of Public Health (PDPH), Philadelphia Fire Department (PFD), Department of Behavioral Health and Intellectual disAbilities, and Managing Director's Office (MDO). These data are not currently linked between departments (we have letters of support from each agency). AR2: the AR2 dispatch and encounter data will be shared from both the PDPH and PFD databases. These data include 1) date, time, and location for all AR2 interactions, 2) demographic information about each participant including name and date of birth, and home address (when available), and 3) information about which components of the AR2 intervention were delivered during each engagement and in follow up.

Data related to linkage to care outcomes will be extracted from the DBHIDS Enterprise Data Warehouse. This data system includes all Medicaid plus uninsured claims for substance abuse treatment and care in Philadelphia. There is robust Medicaid penetration among opioid users in Philadelphia. In 2017, there were over 15,000 unique beneficiaries with opioid use disorder using behavioral health services, up from 9,000 in 2010. DBHIDS has committed to sharing these data in a manner that can be linked to EMS and

AR2 visit. This ensures that we will be able to track the substantial number of people who use opioids and who remain in Philadelphia through the behavioral health system after they have come into contact with the AR2 or EMS.

Data regarding fatal opioid overdose will come from the PDPH through the Philadelphia Office of the Medical Examiner, which sits within the PDPH. These data will include the name, date of birth, and death location for all fatal opioid overdose victims. The second distal outcome is non-fatal overdose, data which will come from both the PFD and the PDPH. The PFD will provide data for all EMS overdose related encounters, including date, time, and location of the dispatch; patient name and date of birth; patient home address (when available); and outcome of encounter (refused transport vs. transport to a hospital).

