- b. **Paired encounter analysis.** For the analysis of paired encounters (one AR2 and a non-AR2 occurring while the AR2 was on another call), we will use an exact McNemar's test for paired data for 0/1 outcomes (death, relapse) and a Cox proportional hazards model for paired data for censored time to event outcomes (time to treatment linkage, time to subsequent overdose). For each AR2 encounter we try to identify a non-AR2 encounter at the same time period within the AR2 response zone. If we find one, these pair of encounters are labeled as a pair and we will follow the patients for 60 days for linkage and non-fatal overdose, and 24 months for fatal overdose, and record outcomes. If multiple non-AR2 encounters happen simultaneously, then conditional logistic regression and stratified Cox models will extend the analysis from a 1-to-1 pairing to a 1-to-many matching. For our power calculations we assume a 1-to-1 pairing, a one-sided test for a reduction in adverse outcomes with  $\alpha = 0.05$  and a power level of at least 0.80. To detect a 50% reduction in the death rate attributable to the AR2 (assumed reduction from 10% to 5%), we need 370 pairs of encounters. To detect a 50% reduction in the rate of repeat non-fatal overdoses (from 30% to 15%), we need 105 pairs of encounters. To detect a 50% reduction in the hazard rate of time to subsequent overdose (equivalent to roughly 19% having a subsequent overdose within one year to 9.5%), we need 200 pairs of encounters. To detect an increase of 50% in the odds of seeking treatment within 60 days of an overdose (from 26% seeking drug treatment after an overdose within 60 days to 35% with AR2), we need 360 pairs of encounters.

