- c. **Comparisons across time discontinuities.** For outcomes underpowered with a paired analysis, we will compare AR2 encounters during AR2 operational hours (10AM-6PM) to non-AR2 encounters outside of AR2's operational hours (6PM-10AM) within the Kensington zip code. Since comparison encounters will not be occurring at the same times as the AR2 encounters, there is a risk of confounding. We will first assess whether AR2 and non-AR2 patients encountered differ on likely confounders (e.g. age, race, sex, substance use profile such as type of drug, injected or not). Ideally focusing exclusively on patient encounters closest to AR2 time boundaries (near 10AM and 6PM) will provide sufficient observations and minimize the risk of confounding. If we find no differences (e.g. patients overdosing earlier in the day resemble those who overdose later in the day) then we will analyze the data as a simple binomial test of proportions (for 0/1 outcomes) or estimate the hazard ratio (for time to event outcomes). If we do find differences, then we will propensity score reweight comparison cases on age, sex, race, and substance use profile so that they do match. The following power calculation assumes no propensity score reweighting, but if propensity score reweighting is needed, the effective sample size, computed as  $(\sum w_i)^2 / \sum w_i^2$  where  $w_i$  is the propensity score weight, will need to equal the needed sample size in the power analysis. This depends on how many comparison encounters closely resemble the AR2 patients. To detect a 50% reduction in the death rate

attributable to the AR2 (assumed reduction from 10% to 5%), we need 380 encounters in each arm. To detect a 50% reduction in the rate of repeat overdoses (from 30% to 15%), we need 105 encounters in each arm. To detect a 50% reduction in the hazard rate of time to subsequent overdose (equivalent to roughly 19% having a subsequent overdose within one year to 9.5%), we need 200 encounters in each arm. To detect an increase of 50% in the odds of seeking treatment within 60 days of an overdose we need 380 encounters in each arm.

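### Treatment linkage is not separated from treatment already under way at the index overdose, so continuing care can count as linkage, diluting the AR2 contrast and, in the day/night comparison, possibly biasing it

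*Protocol*

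**What the plan says.** Treatment linkage, as a rate and as a time, is the proximal outcome of Aim 1 (1.1; 3.1, Aim 1, study design). Section 3.1 describes AR2 as referring patients who refuse transport to a facility with immediate availability and taking them there, so its purpose is to start treatment.

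The outcome data come from the DBHIDS warehouse, described in 4.4: "This data system includes all Medicaid plus uninsured claims for substance abuse treatment and care in Philadelphia". Section 5.5 follows patients for 60 days for linkage. It analyses 0/1 outcomes in pairs ("we will use an exact McNemar's test for paired data for 0/1 outcomes") and time to linkage in a paired Cox model. The planning effect is "an increase of 50% in the odds of seeking treatment within 60 days of an overdose", given as "from 26% seeking drug treatment after an overdose within 60 days to 35% with AR2", for which "we need 360 pairs of encounters". The same effect needs 380 encounters per arm in the time-discontinuity design and 700 per area and period in the difference-in-difference design.

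The exclusions in 2.3 cover age, non-overdose calls, death at scene and repeat encounters. None concerns current treatment. The time-discontinuity design checks example confounders, "age, race, sex, substance use profile such as type of drug, injected or not", and then reweights on age, sex, race and substance use profile. Prior treatment is in neither list.

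**The concern.** Take three patients under this outcome. One has regular treatment claims before the overdose and another claim a few days after it. One is not in treatment and enters a program on day 20. One never enters. The first two both score as linked, and the first scores as the faster success, although that claim only continues existing care.

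Three things are at stake:

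- **Dilution.** Such patients add similar events to both arms and pull the odds ratio and hazard ratio toward 1.
- **Timing.** In the Cox model their claims are among the earliest events, whether or not AR2 attended.
- **Bias.** Treatment status at the overdose is likely to be a strong predictor of a claim within 60 days. If it differs between daytime and night-time patients, the difference passes into the linkage contrast, and the listed weights do not target it.

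**Working it through.** **Inputs from 5.5 (Aim 1, b).** Control rate 26%; odds ratio 1.5; 360 pairs; "we assume a 1-to-1 pairing, a one-sided test for a reduction in adverse outcomes" at alpha 0.05; "a power level of at least 0.80". The share of patients in treatment at the index overdose, q, is not in the document, so every q below is an assumption.

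**The plan's figure.** Odds 0.26/0.74 = 0.3514; times 1.5 = 0.5270; so p2 = 0.3451 (the protocol rounds to 35%). With independent pair members:

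- p10 = p2(1 − p1) = 0.2554 and p01 = p1(1 − p2) = 0.1703
- ψ = p10 + p01 = 0.4257 and δ = p2 − p1 = 0.0851
- n = [1.645√ψ + 0.842√(ψ − δ²)]² / δ² = 361.0, so 362 pairs

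A two-proportion formula gives 359 per arm. McNemar power at 360 pairs is 0.80 by the normal approximation. The exact test gives 0.78 at 34.5% and 0.82 at 35%. The 360 reproduces.

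**Dilution.** Suppose a share q always has a claim within 60 days in both arms. The result depends on what the 26% describes.

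- *Reading A:* 26% and OR 1.5 apply to patients not in treatment, and q comes on top. Then p1 = q + (1 − q)0.26 and p2 = q + (1 − q)0.3451.
- *Reading B:* q lies inside the 26%, and OR 1.5 acts only on the rest. The rest have control rate r = (0.26 − q)/(1 − q). Apply OR 1.5 to get r2; then p2 = q + (1 − q)r2.
- *Reading C:* 26% and 35% are already rates for all patients. Nothing changes.

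Example, B at q = 10%: r = 0.16/0.90 = 0.178; r2 = 0.245; p2 = 0.10 + 0.90 × 0.245 = 0.320; observed OR = (0.320/0.680)/(0.26/0.74) = 1.34.

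| q | A: OR | A: power at 360 | A: pairs for 0.80 | B: OR | B: power at 360 | B: pairs for 0.80 |
|---|---|---|---|---|---|---|
| 5% | 1.44 | 0.74 | 424 | 1.43 | 0.70 | 477 |
| 10% | 1.39 | 0.68 | 494 | 1.34 | 0.55 | 699 |
| 15% | 1.35 | 0.63 | 571 | 1.25 | 0.38 | 1,240 |

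At q = 2% in reading A the power is 0.78. The exact test runs 2 to 3 points lower throughout. In reading C power stays at about 0.80.

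**Does restricting to patients not in treatment help?** At q = 10%, 360 pairs leave 324 (360 × 0.90) or 292 (360 × 0.81), depending on whether pairs are lost through one member or either member. Power moves from 0.68 to 0.72–0.76 in A and from 0.55 to 0.63–0.67 in B. In C the undiluted rates are 0.16/0.90 = 17.8% and (0.3451 − 0.10)/0.90 = 27.2%, and power moves from 0.80 to 0.86–0.89.

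**Bias with no AR2 effect at all.** Let the comparator have 26% linked with 5% in treatment, so the rest link at 0.21/0.95 = 0.2211. If the AR2 group has 10% in treatment, its rate is 0.10 + 0.90 × 0.2211 = 0.2989 and the odds ratio is (0.2989/0.7011)/(0.26/0.74) = 1.21. With 10% in the comparator (still 26% linked) and 5% in the AR2 group, it is 0.80.

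**The case against.** The protocol nowhere says that any claim counts as linkage. It names a data source and an outcome, and a look-back or episode rule may sit in a statistical analysis plan that is not shown. This stands as a limit on the point: continuing care counting as linkage is what follows if only the protocol is applied, not a rule it states. But the protocol itself fixes the source, window, event rate, sample sizes and reweighting set for linkage, and a new-episode rule would change eligibility and the baseline rate, so the gap belongs here too.

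A reader might infer that the 360 pairs are wrong or that power is well below 0.80. The document does not support that. The figure reproduces, the share in treatment is unknown, and under reading C there is no loss. Section 3.1 also says these patients typically lack access to treatment where they live or use drugs, which may point to a small share.

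The model assumes that everyone in treatment has a later claim. Some will have dropped out and could be re-linked by AR2, and restriction would discard that effect. This stands, and it is why stratification is offered as an alternative.

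The confounders to be checked are given as examples, so prior treatment could be added to the check. The reweighting list is not open in that way. Both lists belong to the day/night design. For simultaneous pairs, section 3.1 argues that EMS-only status is largely set by timing and location, and no imbalance is shown, so the bias concern is confined to the day/night comparison.

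**Conclusion.** The point holds in a limited form. Nothing in the protocol separates a new treatment episode from care already under way, so patients already in treatment can count as linked, and early, regardless of AR2.

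The size cannot be fixed from the document. With an assumed 10% in treatment, a claim from all of them, and an odds ratio of 1.5 only among the others, power at 360 pairs is about 0.55 to 0.68. With 26% and 35% as whole-population rates it stays at about 0.80. The bias mechanism does not depend on that choice: an assumed 5% versus 10% imbalance alone gives an odds ratio of about 1.21 or 0.80. Restriction raised power in all three readings at 10%, though in readings A and B it does not bring it back to 0.80. The change should be made, but the stated sample size is not an arithmetic error.

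**What to change.** 1. Use the same DBHIDS data to identify treatment claims in a fixed look-back before the index overdose, with its length set in advance (30 days is one possibility).
2. Base the linkage analyses, 0/1 and time to event, on the opening claim of a new episode among patients without such claims, or stratify by treatment status at index. Report those already in treatment separately.
3. Add prior treatment to the variables checked and reweighted in the time-discontinuity design.
4. State which population the 26% describes, and restate the linkage sample sizes (360 pairs, 380 per arm, 700 per area and period) on that basis. At an assumed 10% in treatment, 360 eligible pairs would need 400 pairs (360/0.90) to 445 (360/0.81) before screening.

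The cost is protocol wording, a look-back extract from a warehouse already being queried, somewhat fewer patients in the linkage analysis, and an estimand limited to new linkage.

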## **2.5. Early Withdrawal of Subjects: N/A**

## **2.6. Vulnerable Populations: N/A**

## **2.7. Populations vulnerable to undue influence or coercion: N/A**

# **3. STUDY DESIGN:**

## **3.1. Design:**

**AIM 1: Determine the effectiveness of the Resilience Project AR2 on opioid overdose outcomes for EMS patients who refuse hospital transport after overdose.**

a. **Rationale and theoretical framework:** Commonly, in Philadelphia and elsewhere, people who refuse transport to an ED after their overdose are at particular risk for repeat overdose and death as they typically do not receive, at the time of the event, referral to treatment, counseling, or take-home naloxone that could be obtained through “warm handoff” programs at the hospital. This gap in prevention and treatment may contribute to significant levels of morbidity and mortality. The AR2 targets this unique and high-risk group of opioid users at the time and place of their overdose. Our evaluation of the AR2 will be guided by the Quality Framework for Emergency Treatment of Opioid Use Disorder as outlined by Samuels and colleagues. In this framework, emergency care harm reduction interventions and treatment can be implemented and evaluated through a Donabedian structure-process-outcome perspective to assess a prehospital emergency approach to opioid use. In Figure 7 we adapt this framework to the AR2 in which high quality prehospital care has the structural capacity to provide take-home naloxone and referral to evidence based treatment programs with immediate availability, harm reduction and treatment referral processes are delivered with high fidelity, and people who overdose are linked to care and subsequently are less likely to experience non-fatal and fatal overdose outcomes.

- b. **Study design:** This quasi-experimental evaluation of the effectiveness of the AR2 will compare rates and time to treatment linkage, non-fatal overdoses within 60 days, and deaths within 24 months for people in the Kensington neighborhood who overdose, refuse EMS transport, and receive AR2 services with those who refuse EMS transport but for whom the AR2 is not dispatched.

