- d. **Comparator Group:** We will use EMS encounters for drug overdose that do not include AR2 arrival on-scene as a comparator group. There are multiple reasons for an EMS-only patient encounter for overdose, e.g., the 1) call is for an overdose outside of the geographic AR2 dispatch zone; 2) EMS dispatch occurs during an time in which the AR2 is not active (6PM-10AM); the 3) AR2 is not dispatched because an overdose is not presumed based on the dispatcher assessment; the 4) AR2 is unavailable because it is on-scene at another call; or 5) the ambulance and/or patient leaves before the AR2 arrives on-scene. The reasons for a patient to receive EMS-alone are largely determined by timing and location of the overdose as opposed to endogenous patient or provider-level characteristics. We will construct multiple comparison encounters based on these five reasons. Specific decisions will depend on the frequency we observe in our data collection. Ideally, encounters that are non-AR2 because of a competing simultaneous call represent an ideal comparator since they match the AR2 call in terms of time, date, and location. These simultaneous encounters will represent the primary comparators. As a secondary comparator group, we will also construct comparison encounters near a temporal or spatial AR2/non-AR2 boundary. Such discontinuities are also useful for identifying causal effects through a difference or difference-in-difference analysis.

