- b. **Characterize which AR2 components are completed (fidelity).** First, we will use the established AR2 database to characterize which AR2 dispatches result in: 1) dispensation of take-home naloxone, 2) referral to a treatment facility that has immediate availability and can provide MAT, 3) transportation to a treatment facility, 4) family engagement, 5) collection of patient telephone information, and 6) telephone follow up within 7 days of encounter. Last, we will characterize which AR2 dispatches lead to any interaction with the individual who experienced the overdose (as some persons leave the scene after being administered naloxone by police, EMS, or a bystander). AR2 staff record each of these variables in real-time for each AR2 dispatch. Data are imported into a secure database and stored at Philadelphia Fire Department headquarters.

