- d. **Difference-in-difference.** To further protect against confounding, we will compare encounters across times and places simultaneously. If within zip code 19134 those who overdose earlier in the day differ from those who overdose later in the day, but those differences are also reflected in the population outside zip code 19134, then a difference-in-difference analysis can use encounters outside 19134 to learn the expected difference between patients with early overdoses and later overdoses and appropriately adjust the within 19134 estimated treatment effect. For example, let  $\hat{p}_{01} - \hat{p}_{00}$  represent the estimated difference in the rate of seeking treatment for those outside 19134 during AR2 operating hours ( $\hat{p}_{01}$ ) and the rate of seeking treatment for those outside 19134 and outside of AR2 operating hours ( $\hat{p}_{00}$ ). Since the AR2 never operates outside of 19134 this difference captures the expected difference treatment seeking for those who overdose at different time periods. Then the difference-in-difference estimate  $((\hat{p}_{11} - \hat{p}_{10}) - (\hat{p}_{01} - \hat{p}_{00}))$  adjusts the treatment contrast within 19134 ( $\hat{p}_{11} - \hat{p}_{10}$ ) by subtracting off the observed difference by time of day for an untreated sample ( $\hat{p}_{01} - \hat{p}_{00}$ ). In practice, we compute ratios of odds ratios for 0/1 outcomes and ratios of hazard ratios for time-to-event outcomes.
- Because difference-in-difference estimates require estimation of three comparison quantities, the estimates are less precise and have greater sample size demands. We compute the number of encounters needed in each area (within 19134 and outside but near 19134) and time period (AR2 operational hours and AR2 non-operational hours). To detect a 50% reduction in the death rate attributable to the AR2 (assumed reduction from 10% to 5%), we need 600 encounters in each area in each time period. To detect a 50% reduction in the rate of repeat overdoses (from 30% to 15%), we need 170 encounters in each area and time period. To detect a 50% reduction in the hazard rate of time to subsequent overdose, we need 320 encounters in each area and time period. To detect an increase of 50% in the odds of seeking treatment within 60 days of an overdose we need 700 encounters in each area and time period.

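### The fallback time-of-day comparison forms its in-hours arm by AR2 contact and its off-hours arm by the clock, so patients who leave early are dropped from one arm only

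*Protocol*

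**What the plan says.** Section 5.5, Aim 1, item c (comparisons across time discontinuities) covers outcomes underpowered in the paired analysis: "we will compare AR2 encounters during AR2 operational hours (10AM-6PM) to non-AR2 encounters outside of" those hours, within the Kensington zip code. The remedies it offers for confounding are to concentrate on encounters near 10AM and 6PM and, where the groups differ, to reweight the comparison cases on age, sex, race and substance use profile.

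Section 3.1, Aim 1, item d defines who is non-AR2: "We will use EMS encounters for drug overdose that do not include AR2 arrival on-scene as a comparator group". Among five reasons for EMS-only care it lists reason 3, "AR2 is not dispatched because an overdose is not presumed based on the dispatcher assessment"; reason 4, the AR2 is busy on another call; and reason 5, "the ambulance and/or patient leaves before the AR2 arrives on-scene". It describes the reasons as "largely determined by timing and location of the overdose as opposed to endogenous patient or provider-level characteristics". Item b defines the contrast as people who overdose, "refuse EMS transport, and receive AR2 services with those who refuse EMS transport but for whom the AR2 is not dispatched".

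Section 3.1, Aim 3, item b notes that AR2 dispatches do not always lead to an interaction, "as some persons leave the scene after being administered naloxone by police, EMS, or a bystander".

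**The concern.** A clock boundary supports a causal comparison when the clock decides who is in each arm. Here the clock decides only the off-hours arm. Entry to the in-hours arm also requires that the call triggered a dispatch, that the unit was free, and that the patient was still there when it arrived. No such conditions apply at night, and nobody can tell which off-hours patients would have left before an AR2 that was not running.

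Reason 5 depends partly on what the patient does, and reason 3 on how the case presents, so neither fits comfortably under the premise that EMS-only status is mainly a matter of time and place. Willingness to stay on scene could plausibly be related to willingness to enter treatment. If it is, part of the observed difference in linkage would reflect who was reached rather than what the AR2 did. This design is the named route for any outcome the pairs cannot power, so it could carry a reported Aim 1 result.

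**Working it through.** **1. Who falls where, by section 3.1 item d and section 5.5 item c**

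| Refusal encounter in the zip code | 10AM–6PM | 6PM–10AM |
|---|---|---|
| Reached by AR2 | AR2 arm | not applicable |
| Left before AR2 arrival (reason 5), or would have left | neither arm | comparator |
| Not presumed overdose at dispatch (reason 3) | neither arm | comparator, unless the inclusion criteria remove it |
| AR2 busy (reason 4), or would have been | neither arm | comparator |

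Reason 4 is close to random. Reason 3 depends on a reading discussed under the objection. Reason 5 is one-sided under any reading, for patients who refuse transport and leave after EMS contact but before the AR2 arrives.

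**2. The stated sample sizes reproduce.** Inputs (section 5.5, items b and c): one-sided α = 0.05, power 0.80, and 26% treatment seeking with the odds raised by half, so 0.26/0.74 × 1.5 = 0.527 and p₂ = 0.527/1.527 = 34.5%. Using n = [z_α√(2p̄(1−p̄)) + z_β√(p₁(1−p₁)+p₂(1−p₂))]²/d² with the continuity correction:
- Treatment seeking: 383 per arm (stated 380).
- Death, 10% to 5%: 382 (stated 380).
- Repeat overdose, 30% to 15%: 108 (stated 105).
- Time to overdose, HR 0.5, Freedman: 56 events; 56/(0.19 + 0.095) = 197 (stated 200).

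These figures are not in error.

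**3. Size of a pure selection effect.** Assume no AR2 effect and 26% linkage in the full population at both times of day. Let s be the share missed and k the linkage rate of the missed relative to those reached. The protocol gives neither s nor k; both are assumptions. Linkage in those reached is 0.26/[(1−s) + s·k].

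| s | k | AR2 arm | Difference from 26% | Odds ratio |
|---|---|---|---|---|
| 0.10 | 0.75 | 26.7% | +0.7 points | 1.03 |
| 0.20 | 0.50 | 0.26/0.90 = 28.9% | +2.9 | 1.16 |
| 0.30 | 0.50 | 0.26/0.85 = 30.6% | +4.6 | 1.25 |
| 0.30 | 0.25 | 0.26/0.775 = 33.5% | +7.5 | 1.44 |
| any | 1.00 | 26.0% | 0 | 1.00 |
| 0.20 | 1.50 | 0.26/1.10 = 23.6% | −2.4 | 0.88 |

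Against the planned 9 points (26% to 35%), the two middle scenarios are 2.9/9 = 32% and 4.6/9 = 51%. With 380 per arm, the one-sided 5% test without continuity correction would reject a true null about 23% and 41% of the time in those two scenarios.

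**4. Cost of forming the in-hours arm by the clock.** If a share f of in-hours patients is missed and gains nothing, the in-hours rate is p₁ + (1−f)(p₂−p₁). Required encounters per arm, by the formula in step 2:

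| f | Treatment seeking | Death | Repeat overdose |
|---|---|---|---|
| 0 | 383 | 382 | 108 |
| 10% | 466 | 479 | 135 |
| 20% | 582 | 617 | 172 |
| 30% | 749 | 820 | 227 |

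**The case against.** Much of the case on the other side stands.

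- **Calls not presumed overdose.** A reader might infer that these are certainly lost from one arm only. Sections 2.2 and 3.1 do not settle it. Both groups must be presumed overdoses to be included, and Aim 1 item c uses presumed overdose as the AR2 dispatch trigger. On that reading such calls leave both arms. Item d points the other way by counting them among EMS-only encounters. The text is ambiguous.
- **Difference-in-difference.** A reader might infer that item d of section 5.5 inherits the flaw. It reasons that "Since the AR2 never operates outside of 19134 this difference captures the expected difference treatment seeking for those who overdose at different time periods" and counts encounters by area and time period. On its face that forms all four cells by place and clock, which is sound. The problem would carry over only if the in-hours 19134 cell were limited to patients reached, and the protocol does not say that it is.
- **Direction.** A reader might infer that the estimate is known to favour the AR2. The documents do not say how many leave or how they fare, so the bias may be zero or may run against the AR2.
- **Scope.** The comparison is a declared fallback behind the paired analysis, and the protocol concedes some added confounding. Restricting to refusers removes, from both arms, ambulances that left with a patient.
- **Estimand.** Specific Aim 1 asks about patients who receive AR2 engagement, and an all-in-hours contrast answers a diluted question.

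None of this repairs the one-sided loss of leavers. Working near the boundary hours and reweighting on four patient features address time-of-day differences, not who was still on scene.

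**Conclusion.** The point holds for the time-of-day comparison. Its two arms are formed by different rules, and in-hours refusers who left before the AR2 arrived are removed from one arm only. The same is true of calls not presumed overdose unless that criterion is applied as the dispatcher's presumption in both arms. Bias follows if the missed patients differ in prognosis, and the listed covariates cannot correct it.

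The size is unknown. The shift of 2.9 to 4.6 points in linkage rests on an assumed 20% to 30% missed, half the linkage rate in the missed, and the same underlying rate by day and night. Because this is a fallback analysis with a bias of unknown direction, it should be fixed, but it does not undermine the trial's preferred analysis or the stated sample sizes.

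**What to change.** In section 5.5, Aim 1, item c, compare all eligible refusal encounters in the zip code from 10AM to 6PM, reached or not, with all eligible refusal encounters from 6PM to 10AM. Apply the same presumed-overdose rule to both arms, by dispatch code if that field is available. In item d, state that all four difference-in-difference cells follow this rule, including the in-hours 19134 cell.

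Report the share of the in-hours arm reached, and keep the AR2-reached contrast as a labelled secondary analysis, which preserves the question in Specific Aim 1. Scale by the share reached only on the risk-difference scale, under the stated assumption that operating hours affect outcomes only through AR2 contact. Simple division is not valid for odds ratios or hazard ratios.

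**Cost.** The change is mostly wording and a selection query on EMS data the protocol already calls for. The EMS fields listed in section 4.4 do not name a dispatch code, so its availability must be confirmed. The main price is dilution. Either restate the encounters needed (for treatment seeking, about 582 per arm at 20% missed and 749 at 30%, against 380), or state the larger effect that the planned number can detect. At 380 per arm the detectable difference is 8.54 points, which means 8.54/0.8 = 10.7 points in those reached at 20% missed and 8.54/0.7 = 12.2 points at 30%.

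Section 3.1 expects 600 to 1,000 engagements over two years. If these are patients reached, the in-hours pool would be 600/0.8 = 750 to 1,000/0.8 = 1,250 at 20% missed, or 857 to 1,429 at 30%. That covers the treatment-seeking need before the first-encounter and near-boundary restrictions. At 30% missed, the death requirement of 820 leaves little room at the lower end.
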